### Cost analysis

A cost-effectiveness analysis will be also undertaken under a societal perspective to compare the cost of the new intervention versus the usual care, to know the clinical effectiveness and the resource savings for the National Health System [47]. Subsequently, a deterministic sensitivity analysis will be performed to assess the robustness of the results [48].

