## Abstract

**Background:**

Intensive interventions on smoking cessation increase abstinence rates. However, few electronic mail (E-mail) based intensive interventions have been tested in smokers and none in primary care (PC) setting. The aim of the present study is to evaluate the effectiveness of an intensive E-mail based intervention in smokers attending PC services.

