## Methods/Design

### Study design

A randomized controlled multicentric trial to evaluate the effectiveness and the cost effectiveness of a clinical practice guide based intervention, based in six contacts (two face to face interviews and 4 E-mails), to obtain continued smoking abstinence at 6 and 12 months compared to brief advice in smokers attended in Primary Care.

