### Description of the intervention

#### Control group

Subjects assigned to the control group, once the motivating problem of the clinical visit had been solved, will receive a brief advice on quitting smoking. Three months after the intervention a second face to face interview will be done to this group to check tobacco abstinence.

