### Outcome measures

#### Main outcome measure

Self reported ‘continuous abstinence’ defined by Hughes et al. 2003 [43] as *the abstinence between quit day and a follow*-*up time* (at six and twelve months) after intervention confirmed by a breath CO cooximetry concentration of 6 parts per million (ppm) or less in standard conditions.

*Other outcome measures*:

– Point prevalence abstinence according to Hughes et al. 2003 [43] defined as *prevalence of abstinence during a time window immediately preceeding follow*-*up* at three, six and twelve months after intervention confirmed by breath carbon monoxide cooximetry in standard conditions.

Self reported tobacco consumption at three, six and twelve months after intervention: daily consumption in cigarettes/day.

– Self-reported reduction of daily tobacco consumption in cigarettes/day when the subject does not stop smoking at three, six and twelve months after intervention.

– Change of stage in the Prochaska and DiClemente's Stages of Change Model at three, six and twelve months after intervention.

– Prescription of tranquilizers, antidepressants, NRT (nicotine replacement therapy), at the beginning and end of the intervention and six and twelve months post intervention.

– Registered use of sanitary services in primary and specialized care, both in public and private settings.

– Time used by professionals in the two face to face interviews (initial and three months visits).

– Time used by sanitary professionals in case they have to answer E-mail contacts.

– Time used by patients in case they have to ask questions during the E-mail intervention.

– Costs for the patients to access Primary Care service at three, six and twelve months after intervention.

*Independents*:

– Type of intervention: Intensive counseling by E-mail vs brief advice.

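### The only uncertainty method named for the cost-effectiveness result is a deterministic sensitivity analysis, which does not give the joint sampling uncertainty of cost and abstinence

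*Protocol article*

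**What the plan says.** The Study design section of the protocol article says that the trial is "to evaluate the effectiveness and the cost effectiveness of a clinical practice guide based intervention". The abstract is narrower: "The aim of the present study is to evaluate the effectiveness of an intensive E-mail based intervention in smokers attending PC services".

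The Cost analysis section consists of two statements. The first sets the analysis and its viewpoint: "A cost-effectiveness analysis will be also undertaken under a societal perspective to compare the cost of the new intervention versus the usual care". The second gives the treatment of uncertainty: "a deterministic sensitivity analysis will be performed to assess the robustness of the results". No other uncertainty method is named for the economic result.

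The list of other outcome measures includes economic quantities recorded in the trial: use of health services, professional time, patient time, and "Costs for the patients to access Primary Care service at three, six and twelve months after intervention".

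The Statistical methods section plans group comparisons, repeated-measures covariance analysis, and multilevel logistic and Poisson regression. These are applied to the dependent variables one by one, with two-tailed tests at 0.05.

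**The concern.** A cost-effectiveness ratio from a trial divides a difference in mean cost by a difference in abstinence. Both are estimated from the same patients, both carry sampling error, and the two errors may be correlated. A deterministic sensitivity analysis shows how the result moves when the analyst changes chosen inputs. It is well suited to unit prices and other assumptions. It attaches no probability to the range it shows, and it does not combine the sampling error of cost with that of effect.

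At stake is how firmly the trial can speak about value for money. The article expects lower costs and refers to savings for the health system. If the ratio is reported with deterministic ranges alone, a reader cannot tell how far chance in the patient sample could move it.

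**Working it through.** **Inputs.** From the Sample size section: 5% continued abstinence in the control group, a difference of 5 points (hence 10% with the intervention), two-sided alpha 0.05, power 0.80, 20% dropout, 530 per arm. From the section on inclusion and randomization: 1:1 allocation. The article gives no cost figures.

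**Step 1: reproduce the plan's own figure.** With the arcsine formula, h = 2[arcsin √0.10 − arcsin √0.05] = 0.1925, and n = 2(1.960 + 0.842)² / h² = 424 per arm. Inflating for dropout, 424 / 0.80 = 530 per arm, or 1060 in total. This matches exactly, so the sample size is not in question and 5% vs 10% is the right reading of the plan.

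**Step 2: sampling error of the effect, 530 per arm.**
- SE = √[(0.05 × 0.95 + 0.10 × 0.90) / 530] = √(0.1375 / 530) = 0.0161.
- 95% interval: 0.05 ± 1.96 × 0.0161 = 0.0184 to 0.0816, that is, 1.8 to 8.2 points.

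**Step 3: carry this into the ratio.** Let D be a positive cost difference per patient, treated as known exactly. Cost per extra quitter = D / effect.
- Point estimate: D / 0.05 = 20 D.
- Limits: D / 0.0816 = 12.3 D and D / 0.0184 = 54.3 D.
- Span: 54.3 / 12.3 = 4.4-fold.

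**Step 4: the same with completers only.** 530 × 0.80 = 424 per arm.
- SE = √(0.1375 / 424) = 0.0180; interval 1.5 to 8.5 points.
- Limits: 11.7 D and 68.0 D; span 68.0 / 11.7 = 5.8-fold.

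**Step 5: let the costs vary too (illustration on assumed costs).** Assume mean costs of 150 and 100 arbitrary units and gamma-distributed costs, drawn independently of abstinence. The point ratio is 50 / 0.05 = 1000. The central 95% of 20,000 simulated trials gives:

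| Per arm | Coefficient of variation of cost | Range of the ratio | Span |
|---|---|---|---|
| 530 | 0.5 | about 590 to 2670 | 4.5-fold |
| 530 | 2 | about 360 to 2930 | 8.2-fold |
| 424 | 0.5 | about 560 to 3410 | 6.1-fold |
| 424 | 2 | about 300 to 3670 | 12.3-fold |

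In these cases the fixed-cost spans in steps 3 and 4 understate the total uncertainty, by little when costs vary little and by more when they are skewed.

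**Step 6: can the named methods give this?** The deterministic analysis can move the effect between its limits, as step 3 does, but it gives no interval that combines cost and effect. The tests and regressions under Statistical methods can give the error of abstinence and of each cost-related outcome separately, but not of their ratio.

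**The case against.** The strongest reply is that the Cost analysis section is a short summary in a journal article. It does not say that the deterministic analysis is the only treatment of uncertainty, and a fuller plan could add a bootstrap and an interval. That stands as a limit on the wording: a reader might infer that the trial will report no interval, and the article does not say so. It does not remove the point. The article is not silent on robustness; it names a method and gives it that task, and the method does not fit sampled data on its own.

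Second, deterministic does not mean one input at a time, and a deterministic analysis may run the effect over its confidence limits. This is correct, and such an analysis would reveal the 4.4-fold spread. It would still not give a joint interval.

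Third, sampling error is not ignored altogether, because the outcomes are tested separately. This also stands; what is lacking is the joint uncertainty.

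Three stronger readings are not supported:
- A reader might take cost-effectiveness to be a main aim. The abstract and the closing Discussion paragraph state effectiveness only, and the main outcome is abstinence. It is a co-stated aim.
- A reader might infer a ratio with a denominator close to zero. At 5% vs 10%, the only rates in the article, the lower limit is 1.8 points (1.5 with completers). An almost unbounded ratio needs a smaller effect than the plan assumes.
- A reader might infer that the comparator's cost is inflated by a research visit, since after three months "a second face to face interview will be done to this group to check tobacco abstinence" and professional time at that visit is a listed outcome. No section says that this visit will be costed as usual care or that checking abstinence is its sole purpose. Removing its cost while keeping any effect it had on quitting would itself be a debatable choice.

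**Conclusion.** The point holds in a limited form. The article makes cost-effectiveness a co-stated object of the trial, collects the data for it within the trial, and names only a method that cannot express the joint sampling uncertainty of the ratio. On the plan's own rates, the abstinence difference alone makes the cost per extra quitter uncertain by about 4.4-fold with 530 per arm and about 5.8-fold with 424.

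These figures assume that the planned 5% vs 10% is observed, a normal approximation, independent patients, and a cost difference that is positive and known exactly. The wider ranges in the table rest on assumed costs and are illustrative. The sample size and the primary abstinence analysis are not affected.

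**What to change.** In the Cost analysis section, add a non-parametric bootstrap that resamples each patient's cost and abstinence together, within arm, and allows for clustering by professional. Report an interval for the incremental ratio or for net benefit, and an acceptability curve. Net benefit is the safer scale if the effect turns out small, because it has no denominator. Keep the deterministic sensitivity analysis for unit prices and other assumptions, and say that this is its purpose.

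The cost is a little more analysis on data that the trial already plans to collect. The price in presentation is a ratio that looks less certain than a point estimate with deterministic ranges.

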### Sample size

Accepting an alpha risk of 0.05 and a beta risk of 0.20 in a bilateral contrast, 1060 individuals are needed; 530 individuals in the IG and 530 in the CG in order to detect a difference of at least a 5% among both groups. A continued abstinence of 5% was assumed for the non intervention group and a dropout rate of 20% is estimated. The sample size calculations were performed with the Granmo program (version 7.1).

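### The one robustness method named for the cost-effectiveness aim, a deterministic sensitivity analysis, does not carry the joint sampling error of the cost and abstinence differences

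*Protocol article*

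**What the plan says.** Study design gives the trial's purpose as "to evaluate the effectiveness and the cost effectiveness of a clinical practice guide based intervention", so the economic question stands beside the clinical one.

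Cost analysis has two sentences of method. The first sets the type and viewpoint: "A cost-effectiveness analysis will be also undertaken under a societal perspective to compare the cost of the new intervention versus the usual care". The second gives the approach to uncertainty: "a deterministic sensitivity analysis will be performed to assess the robustness of the results". It does not say which inputs are varied, over what ranges, or whether singly or together. It does not define the summary measure, and it neither names nor rules out any other method.

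The outcome list shows that the economic inputs come largely from trial participants. It includes "Costs for the patients to access Primary Care service at three, six and twelve months after intervention", registered use of health services, professional time and patient time, alongside CO-confirmed abstinence.

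Statistical methods plans multilevel logistic and Poisson regression for each dependent variable. That gives separate inference on individual outcomes. It does not link costs and effects.

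**The concern.** A deterministic sensitivity analysis replaces inputs with chosen alternative values and recomputes the answer. It suits inputs that are not sampled, such as unit prices. In this trial the two quantities that drive the result, the arm difference in cost and the arm difference in abstinence, are estimates from the same patients. Each has a standard error, and the two may be correlated because a patient's cost and outcome can be related. A deterministic analysis yields no joint distribution of the two, so it gives neither an interval for the cost-effectiveness result nor a probability that the intervention is cost-effective.

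At stake is how the economic conclusion reads. The Discussion hopes to offer the intervention to primary care and other health settings. A result described as robust on deterministic grounds alone could be taken as firmer than a trial of this size can make it.

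**Working it through.** **Inputs from Sample size.** Two-sided alpha 0.05 and power 0.80 ("Accepting an alpha risk of 0.05 and a beta risk of 0.20 in a bilateral contrast, 1060 individuals are needed"); equal arms of 530; control abstinence 5%; a 5-point difference ("in order to detect a difference of at least a 5% among both groups", read as 5% against 10%); dropout 20%.

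**Reproducing the plan's figure.** Arcsine formula: n = 2 × [(1.960 + 0.842) / (2·asin√0.10 − 2·asin√0.05)]² = 2 × (2.802 / 0.1925)² ≈ 424 per arm. Then 424 / 0.80 = 530 per arm and 1,060 in total, which matches exactly.

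**Sampling error of the abstinence difference.** SE = √[(0.05 × 0.95 + 0.10 × 0.90) / n] = √(0.1375 / n). The number treated per extra quitter is 1 / difference, which is 20 at the design effect. It is also the multiplier that turns a cost difference into a cost per extra quitter.

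| Analysed per arm | SE (points) | 95% interval (points) | Treated per extra quitter | Spread |
|---|---|---|---|---|
| 424 | 1.80 | 1.5 to 8.5 | 11.7 to 68.0 | 5.8-fold |
| 530 | 1.61 | 1.8 to 8.2 | 12.3 to 54.3 | 4.4-fold |

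The 530 row takes the same two rates to hold among all randomised patients. If 3 points were observed with 424 per arm (5% against 8%), then SE = √[(0.0475 + 0.0736) / 424] = 1.69 points. The interval is −0.3 to 6.3 points, and the ratio has no finite upper limit.

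**Adding cost error (assumed values; the documents give none).** Take a cost difference of 50 units, 424 per arm, zero correlation, and normal sampling errors in 400,000 draws. The ratio is 50 / 0.05 = 1,000. Its central 95% range by assumed per-patient cost SD is:

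- SD 0: 580 to 3,232
- SD 100: 529 to 3,281
- SD 300: 164 to 3,616
- SD 600: −718 to 4,485

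**What confidence-limit substitution would show (SD 300).** The cost SE is 300 × √(2/424) = 20.6, so the cost limits are 50 ± 1.96 × 20.6 = 9.6 to 90.4.

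- Cost varied alone: 9.6 / 0.05 to 90.4 / 0.05 = 192 to 1,808.
- Abstinence varied alone: 50 × 11.7 to 50 × 68.0 = about 585 to 3,400.
- Both at opposite extremes: 9.6 / 0.0853 to 90.4 / 0.0147 = about 113 to 6,150.
- Joint sampling range: 164 to 3,616.

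None of the three deterministic ranges matches the joint one, and none uses the correlation. The SD 0 range differs slightly from abstinence varied alone because about 0.3% of draws have an abstinence difference at or below zero.

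**The case against.** The strongest reply is that the Cost analysis section is a short summary in a journal article. It cites sources for its methods and says that a deterministic analysis will be done, not that nothing else will be. A reader might infer that the result will be tested by this method and no other. The text does not support that, because no other method is excluded and a fuller plan may add one. What stands is narrower: robustness of a stated aim is tied to one named method, and that method does not match the kind of data collected.

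A reader might also infer that a deterministic analysis must hold the arm differences fixed and hide all sampling error. That is too strong. It can set the abstinence difference to its 95% limits, and the 11.7 to 68.0 range above is that very calculation. Abstinence and the cost items also receive their own inference under Statistical methods. What is missing is the joint step.

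Three further inferences fail. The documents do not show that sampling error is the main source of uncertainty, since they give no figures for price uncertainty. They do not define the result as a cost per extra quitter, although that is a natural reading with abstinence as main outcome. No single range in money can be attached to this trial, because every such range rests on assumed costs.

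It is also fair that the Abstract's aim, the main outcome and the sample size concern effectiveness. That lowers the weight of the point, but Study design still states the economic aim. Finally, patients are randomised individually, so resampling by professional is an option and not a requirement.

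**Conclusion.** The point holds in a limited form. For a cost-effectiveness aim built on patient-level trial data, the one robustness method named does not carry the joint sampling error and correlation of cost and effect, and nothing in Statistical methods supplies that step. The result could look more certain than the data allow; by how much cannot be settled from the documents.

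The size that rests on the trial's own figures is the 4.4-fold to 5.8-fold spread in number treated per extra quitter. It assumes that the planned rates are true and counts abstinence error alone. The money ranges are illustrations. This is worth correcting before the economic analysis is run. It does not affect the clinical comparison.

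**What to change.** Add to Cost analysis, in words such as these: sampling uncertainty will be assessed by a non-parametric bootstrap of patients within arms, keeping each patient's cost and abstinence outcome paired; 95% intervals will be reported for incremental cost and incremental abstinence, together with net monetary benefit over a stated range of willingness to pay, or an acceptability curve. Resampling by professional could be offered as an option, in line with the planned multilevel model. Net benefit or an acceptability curve also stays interpretable when the abstinence difference is near zero, where the ratio does not.

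Keep the deterministic analysis for unit prices and other non-sampled inputs, and state which are varied and over what ranges. Name the summary measure.

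The cost is a few sentences and a little more analysis work on data already planned. The downside is that the reported result will look less certain.

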### Ethical approval

This study has been reviewed and approved by the Clinical Investigation Ethics Committee of the IDIAP Jordi Gol, located in Barcelona, Spain and registered at Clinical Trials (code number: P11/41). The participation in this study is strictly voluntary and withdrawal will not have any consequence on the management of the subject illness, which will be carried out rigorously following the accepted international norms. The data will be treated confidentiality according to the Organic Law which regulates the confidentiality of computerized data (Personal data Protection Law 15/1999); only the investigators and monitors/auditors of the study will have access to the data of the subjects who agreed to participate.

### Associated studies

We are currently undertaking two associated studies to the TABATIC Project. The first, a descriptive one aims to know the availability and use of Communication and Information Technologies among smokers attended in primary care. The second one, a qualitative, intends to find out barriers and facilitators of Communication and Information Technologies to help smokers to quit, that both, smokers and health professionals who help patients to quit smoking, refer.

## Discussion

The proposed intense intervention consists in the application of the recommendations of an evidence-based practical clinical guideline of the Primary Care Division of the Catalan Institute of Health [42] based in six contacts (two face to face interviews and 4 E-mails), to obtain continued smoking abstinence at 6 and 12 months. There are some international studies that use E-mail based interventions to help smokers to quit, but none has the same characteristics as the one proposed [5,10,26,27,32-35,37,49]. Furthermore, to our best knowledge, in Spain there are no studies that use this type of interventions at any level of clinical services.

Since the implementation in 2006 of the law 28/2006 for smoking prevention, the number of primary care consultations regarding smoking cessation has been raised, subsequently an approach to smoking cessation should be a key essential objective of both the clinical practice and public health research. Subsequently, primary care is an ideal setting to develop a health counseling E-mail program based on a practical clinical guideline due to its almost universal coverage in Spain [3,50]; it is estimated that 75% of the population visits his or her general practitioner at least once a year, and that people who smoke do so more often than non-smokers [3,51].

One of the main strengths of the TABATIC project is that, to our best knowledge, for the first time the therapeutic use of E-mail tracking will be evaluated in order to help smokers to quit. Furthermore, the same sanitary professional, who habitually attends the patient and with whom a previous confidence relationship has been established, is the one who follows the patient during this intervention which can lead to more successful outcomes if compared to other more impersonal follow-up interventions such as web pages or community programs [31]. Another strength of E-mail tracking interventions according to Kuppersmith is its *asynchronous nature*; E-mail communication allows physician and patient not to be available at the same time. In addition, both can access at their messages at their own convenience and as many times as needed [21]. Moreover, this type of intervention could reduce social and sanitary costs due to its great accessibility, its capability to diminish trips and timeouts to be attended.

Selection bias among health care professionals may occur since those who volunteered to participate could be more motivated than other sanitary professionals. Randomization will be made among smokers and not in primary care centers which will lead to use this E-mail intervention in only some of his or her patients; however the randomization will be previously automatically created so the professional will not be able to decide on which patients should use the intervention since it will be computer generated. Patients assigned to the control group will receive a brief advice on quitting smoking. One of the main limitations of the study is that we will only include professionals who know how to use computers and E-mail and can assure participation in the study by using it. However we feel confident that an important number of participating professionals will run correctly the program since most of them have previously participated in other complex tobacco studies undertaken in our territory such as the ISTAPS (176 basic care units that worked in 82 Spanish primary care centers; participants: 2,827 smokers aged 14–85 years), ITADI (400 professionals and 1077 diabetic smokers) and BIBE studies (162 pediatric teams from 96 Spanish primary care centers; participants: 1101 child) [12,18,52]. No economic compensation will be offered to sanitary professionals; consequently, those who expect to be reimbursed for this extra activity will be also excluded of the study. Some professionals may be reluctant to use electronic mail in professional health care-patient communication. Reasons to be reluctant may include the believe that written messages can omit important connotations in communication (such as body language or voice tone), the concern that individuals may send a vast number of irrelevant messages and the possible dissemination of health professional e-mail address [21,53]. To assure health care professional and patient confidentiality, an external company will develop and maintain the study a secure web page; if needed, they will control and limit each subject web page use [54]. We are currently carrying out a qualitative study in order to describe possible barriers and facilitators of Information and Communication and Technologies to help smokers to quit.

If the proposed intervention is effective, it should be adapted to the informatics systems of each local health service.

The present trial aims to show the effectiveness of an E-mail smoking cessation intervention based in the recommendations of an evidence-based clinical practice guideline of the Primary Care Division of the Catalan Institute of Health at six and twelve months post-intervention [42]. The goal is to propose a new and effective intervention in primary care, as well as in other sanitary settings, as a complementary tool to treat smokers.

